## 1. Introduction

Sepsis-induced acute respiratory distress syndrome (SI-ARDS) is a common and severe complication of sepsis and is an independent contributor to poor prognosis of patients [1,2]. Acute respiratory distress syndrome (ARDS) is characterized by lung epithelial injury with a decrease of oxygenation index and is manifested as respiratory distress [3]. Once injury to the lung epithelial damage is evidently promoted, the progression to ARDS cannot be reversed, and the mortality rate reaches approximately 40% [4,5]. However, it remains a clinical challenge to identify SI-ARDS early and accurately, something which could optimize treatment strategy and reduce the mortality risk [6]. As such, a novel method for early identification of SI-ARDS is of paramount interest to clinicians and researchers.

Immune dysfunction driving sepsis-induced target organ damage has been fully appreciated and is characterized by excessive inflammatory reaction and immune function inhibition [7,8]. However, despite much significant research that has been undertaken to improve the understanding of ARDS pathogenesis, including viable predictive molecular biomarkers and multigene-based expression assays, early identification for SI-ARDS remains elusive [9,10,11,12,13]. Additionally, the immune microenvironment, influenced by the above mechanisms, has not been quantitatively assessed for the early identification of SI-ARDS, which comprises immune cell subsets, inflammatory cytokine and other components [14,15,16]. Recent studies have revealed artificial intelligence with radiomics emerging as a quantitative imaging method for early detection, risk assessment, and treatment decisions in various diseases [17,18]. Despite the lack of a clear correlation between radiomics and pathophysiology, application of radiomics in predicting SI-ARDS is worth exploring.

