### 2.2. Cohort Descriptions and Definitions

This study will recruit 200 patients in a developing group and 200 patients in a validating group from two hospitals. Patients’ age above 18 years diagnosed as sepsis or septic shock will be screened for eligibility. SI-ARDS is defined by sequential occurrence of the sepsis-3 consensus criteria for sepsis [7] and the Berlin definition for ARDS [2]. Exclusion criteria are (1) admission stay <24 h, (2) patients with end-stage lung disease or long-term oxygen therapy, (3) patients with sepsis or septic shock whose oxygenation index (OI, arterial oxygen tension/inspired oxygen fraction [PaO2/FIO2]) ≤300 mmHg before admission, (4) a history of lung transplantation and chronic obstructive pulmonary disease, and (5) cancer patients who have/have not received chemotherapy. Since sepsis and ARDS are not easy to diagnose, two doctors will separately perform patient inclusion/exclusion criteria, extract the data, and assess the data quality. Any discrepancies will be resolved by consensus, and if necessary, a third professor can be consulted.

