### 2.4. Data Collection

All clinical data will be collected by investigators and trained personnel. Each participant’s data will be filled in electronic case report forms (CRF) and stored online using research electronic data capture (REDCap) [23]. The CRF is designed to collect the necessary information based on this study protocol. The detailed contents of CRF contain four main parts: (1) demographics and chronic disease history (including age, gender, smoking status, hypertension, diabetes mellitus, chronic lung disease and coronary heart disease), (2) laboratory tests and imaging examination (including routine blood, routine biochemistry, coagulation function, arterial blood gas analysis, blood culture, sputum culture, and ID of chest CT), (3) treatment process (including source of infection, anti-infection therapy, ventilator use or not, and type and dose of vasopressor therapy), (4) outcomes (intensive care unit (ICU) stay or not, length of ICU stay, total length of hospital stay, and in-hospital death).

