### 2.6. Outcome Measures

In this study, the primary outcome measure will be occurrence of ARDS, which is defined as pulmonary or nonpulmonary sepsis that had progressed into ARDS.

Secondary outcome measures are as follows:

(1)Grade of pulmonary damage: patients will be classified as mild (200 <  PaO2/FiO2 ≤ 300 mmHg), moderate (100 < PaO2/FiO2 ≤ 200 mmHg), or severe (PaO2/FiO2  ≤  100 mmHg) at the moment of diagnosis of ARDS [2];(2)Ventilator-free days, VFD: defined as the number of days between successful weaning from mechanical ventilation and day 28 after ICU admission;(3)Respiratory organ failure-free days, RFFD: defined as the number of days between a day without evidence of respiratory organ failure [27];(4)28-day mortality: all-cause mortality within 28 days following enrolment.

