## 3. Discussion

Mild ARDS patients, defined with OI ≤ 300 mmHg but >200 mmHg, may not require invasive mechanical ventilation, and the condition is more readily reversible [30]. To date, early lung-protective ventilation strategies with lower tidal volume ventilation that protect the lungs from the progression of injury, have revealed reduced mortality in ARDS patients [31,32]. Although SI-ARDS patients with end-stage refractory respiratory failure can be efficiently treated by venovenous extracorporeal membrane oxygenation (VV-ECMO), surviving patients with severe ARDS may progress to pulmonary fibrosis, resulting in a progressive decline of respiratory function and ending in death [33]. Thus, an early identification and classification of the SI-ARDS is essential to improve patients’ prognosis and disease management.

Until now, OI and radiologic features have been sought as classical indices to identify ARDS in sepsis patients. However, when OI declines and characteristic imaging findings are clearly presented, delays in diagnosis and treatment may be impossible to avoid. Two previous studies have tried to utilize the lung injury prediction score (LIPS) to predict risk for ARDS by collecting routinely available clinical data, but this LIPS model has a relatively low positive predictive value for ARDS and depends on a reliable portable chest radiograph interpretation [6,34]. Other multigene-based expression assays are also currently used to predict early SI-ARDS but their predictive utilities are still restricted in certain patient subsets who are characterized with the “reactive” phenotype [35,36,37].

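### Ventilator-free days run from weaning to day 28 with no rule for death, so a weaned patient who dies scores like a survivor and several expected groups get no score

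*Protocol article*

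**What the plan says.** Section 2.6 lists four secondary outcomes, three of which matter here.

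- Outcome (2), VFD: "defined as the number of days between successful weaning from mechanical ventilation and day 28 after ICU admission".
- Outcome (3), respiratory organ failure-free days (RFFD): "defined as the number of days between a day without evidence of respiratory organ failure", followed by a citation.
- Outcome (4), 28-day mortality: "all-cause mortality within 28 days following enrolment". Its clock starts at enrolment, whereas the VFD clock is tied to ICU admission.

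The population is broader than ventilated ICU patients. Under section 2.2, adults "diagnosed as sepsis or septic shock will be screened for eligibility", and neither ICU admission nor ventilation is an entry condition. The CRF items in section 2.4 include "intensive care unit (ICU) stay or not" and ventilator use as yes or no. The Discussion says that patients with mild ARDS "may not require invasive mechanical ventilation, and the condition is more readily reversible".

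Section 2.7 puts VFD, RFFD and 28-day mortality through LASSO-Cox and RFE-SVM and then Kaplan–Meier estimation. It does not say how death enters the first two.

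**The concern.** Section 2.6(2) fixes both a start and an end for the count, so it can be applied as printed. The result is wrong for some patients and undefined for others. Deaths after weaning earn full credit for days the patient did not live. Deaths on the ventilator, among the worst courses, have no weaning date and drop out. Survivors who never needed a ventilator, the best courses, drop out too. What remains is a score conditional on surviving to be weaned, which is part of what the outcome should measure. A comparison of model-defined risk groups on that score would be biased or shrunk. If the gaps are filled only once the data are known, the scoring choice can drive the result.

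**Working it through.** The documents state no figure for VFD, so there is none to reproduce. The check applies the printed formula to patient courses and then to two groups.

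**1. Individual courses.** Printed: VFD = 28 − weaning day, in days since ICU admission. Comparison rule (an assumption of this review): death by day 28 = 0, still ventilated at day 28 = 0, never ventilated and alive = 28.

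| Course | Printed | Comparison rule |
|---|---|---|
| Weaned day 5, alive at day 28 | 23 | 23 |
| Weaned day 5, dies day 10 (5 days alive off the ventilator) | 23 | 0 |
| Weaned day 35, alive | −7 | 0 |
| Dies on the ventilator | none | 0 |
| Alive, never weaned | none | 0 |
| Never ventilated, alive | none | 28 |
| Never in ICU, unventilated, alive | none (no day 28 exists) | 28 |

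**2. Scale from the article's own rates.** Section 2.3 expects ARDS in 25–50% of patients, so 400 × 0.25 to 0.50 = 100 to 200 cases. The Introduction puts mortality at about 40%, which gives 40 to 80 deaths. If 10–30% of these follow weaning (assumed), 4 to 24 patients would be scored like survivors. The documents do not give the numbers ventilated or in ICU.

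**3. Group contrast under assumed rates.** None of these inputs comes from the documents.

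- Low risk: 25% ventilated; daily weaning hazard w = 0.10; daily death hazard on the ventilator d = 0.02; 5% die after weaning; 5% die if never ventilated.
- High risk: 70% ventilated; w = 0.10, varied down to 0.05; d = 0.05; 20% die after weaning; 10% die if never ventilated.

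Times are exponential, ventilation starts at ICU admission, and the last two kinds of death fall by day 28. With h = w + d, the share of ventilated patients ever weaned is w/h and their mean weaning day is 1/h.

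Printed mean = 28 − 1/h:
- Low: 28 − 1/0.12 = 19.7
- High, w = 0.10: 28 − 1/0.15 = 21.3
- High, w = 0.07: 28 − 1/0.12 = 19.7
- High, w = 0.05: 28 − 1/0.10 = 18.0

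Share with no score = 1 − (share ventilated × w/h):
- Low: 1 − 0.25 × 0.833 = 79%
- High, w = 0.10: 1 − 0.70 × 0.667 = 53%

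Mean under the comparison rule = (never ventilated and alive) × 28 + (share ventilated) × (1 − death after weaning) × X, where X = (w/h) × [28 − (1 − e^(−28h))/h]:
- Low: 0.75 × 0.95 × 28 + 0.25 × 0.95 × 16.63 = 19.95 + 3.95 = 23.9
- High, w = 0.10: 0.30 × 0.90 × 28 + 0.70 × 0.80 × 14.29 = 7.56 + 8.00 = 15.6 (a simulation of 400,000 patients gave 15.5)
- High, w = 0.05: 7.56 + 0.70 × 0.80 × 9.30 = 7.56 + 5.21 = 12.8

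Low minus high is therefore −1.7 (w = 0.10) or +1.7 (w = 0.05) by the printed formula, against +8.3 and +11.1 under the comparison rule.

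**The case against.** The strongest reply is that a reader might infer that the printed formula makes high-risk patients look better. The documents do not support that as a general result. The reversal comes from giving both groups the same weaning hazard: the higher death hazard in the high-risk group then shortens the mean time to weaning among those weaned (1/0.15 = 6.7 days against 1/0.12 = 8.3). At a high-risk weaning hazard of 0.07 the means are equal, and at 0.05 the order is correct. Slower weaning in sicker patients is at least as plausible.

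The reversal also needs never-weaned patients to stay unscored. If they are read as having zero days, which the text does not say, and negative scores are set to 0, the means among ventilated patients are 16.6 v 14.3, in the right order. Crediting deaths after weaning still narrows that gap: with those deaths scored 0, the means are 16.63 × 0.95 = 15.8 and 14.29 × 0.80 = 11.4, so the difference is 4.4 rather than 2.3.

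Four further points stand in part.

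- The unscored shares of 79% and 53% are mostly inputs: 75 and 30 percentage points are the assumed never-ventilated shares.
- Section 2.7 does not plan a comparison of mean VFD by name, so the means only illustrate. Its Cox and Kaplan–Meier steps still need a rule for death and give none.
- Values for never-ventilated and non-ICU patients could sit in a fuller document. The printed start and end of the count would still contradict a death rule placed there.
- Successful weaning is undefined and might carry a short survival requirement, but that would remove only the earliest deaths after weaning.

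On RFFD, a reader might infer a worse defect than in VFD. The sentence is garbled and cites a source that may hold the full definition, so all that can be said is that the printed definition is incomplete.

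**Conclusion.** The point holds, at moderate severity. It follows from the wording alone that a death after weaning scores like survival, that late weaning scores negative, and that deaths on the ventilator, never-ventilated patients and non-ICU patients have no score. Sections 2.2 and 2.4 and the Discussion allow for such patients.

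The size rests on the assumed ventilation, weaning and death rates. In both scenarios the true separation of 8 to 11 days shrinks to less than 2 days in either direction. Whether the order reverses cannot be settled from the documents.

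A reader might also infer that the main result is at risk. It is not: the primary outcome is occurrence of ARDS, and neither it, its AUC evaluation nor the 160-patient calculation uses VFD or RFFD. 28-day mortality is reported separately.

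**What to change.** Rewrite section 2.6(2) so that VFD is the number of days alive and free of mechanical ventilation in a 28-day window. Score 0 for death by day 28 or ventilation still needed at day 28, and 28 for survivors never ventilated. Start the window at one time origin for all 400 patients, in or out of ICU and in both cohorts, and use the same origin for 28-day mortality. State what counts as successful weaning and how a return to ventilation is handled. Complete section 2.6(3) on the same window with the same death rule. Align section 2.7 by naming a method suited to a bounded score, or by analysing weaning with death as a competing event.

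The text change is a few sentences and needs no extra patients. There are two costs. The score becomes a composite with death and has point masses at 0 and 28. Section 2.4 lists ventilator use only as yes or no, so ventilation start and weaning dates must be confirmed in the CRF or added to it, including from the charts of the 200 retrospective patients.

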### 2.7. Statistical Analysis

Continuous variables between two groups will be compared by T test or Wilcoxon rank sum test, whereas categorical variables will be compared by χ^2^ test. Univariate and multivariate logistic regression will predict occurrence of ARDS, using variables that selected by consensus of variable importance ranking by random forest [28] and least absolute shrinkage and selector operation (LASSO) regression techniques [29]. With the selected clinical and radiomics features, we will develop two versions of the ARDS prediction model, using logistic regression (LR) and support vector machine (SVM). Then a prognostic model will be built for prediction of individual and classification of severe level. ROC curves will determine the optimal cut-off point for models, and patients will be divided into high-risk and low-risk groups. VFD, RFFD and 28-day mortality will be screened indicators with LASSO-COX and RFE-SVM algorithm. Thereafter, these will be estimated using the Kaplan–Meier method. All these algorithm performances will be assessed using the AUC and *p*-values less than 0.05 will be considered statistically significant. After these main analyses, other subgroups will be carried out as following: septic shock vs. non-septic shock, and pulmonary sepsis vs. non-pulmonary sepsis. Statistical analysis will be performed using the R programming language, including its packages.

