## 2. Materials and Methods

### 2.1. Study Design

The study was registered with ClinicalTrials.gov (NCT04541264, https://clinicaltrials.gov/show/NCT04541264) on 9 September 2020. In this double-center, ambispective, observational study, we will collect chest CT and clinical information of patients with sepsis and septic shock treated in our hospital (Sun Yat-sen Memorial Hospital, Sun Yat-sen University) and Shenshan Medical Center, Memorial Hospital of Sun Yat-sen University (from 1 May 2015 to 30 May 2022). For the final analysis, 400 patients will be enrolled according to the TRIPOD guideline [19]. Among the 400 patients, 200 will be retrospectively recruited from our hospital from May 2015 to August 2020, 100 patients will be prospectively recruited from our hospital from August 2020 to May 2022, and the other 100 patients will be prospectively recruited from Shenshan Medical Center, Memorial Hospital of Sun Yat-sen University from August 2020 to May 2022. One hundred-sixty patients of the retrospective cohort will be selected as a discovering group to reconstruct the model, and 40 patients of the retrospective cohort will be selected as a testing group for internal validation. Additionally, 200 patients of the prospective cohort will be selected as a validating group for external validation. Follow-up of the relevant patients will be conducted until April 2023. This study was approved on 19 August 2020 by the Ethics Committee of Sun Yat-sen Memorial Hospital, Sun Yat-sen University, Guangzhou, China. Figure 1 shows the flow chart of the study protocol.

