Recently, artificial intelligence-based radiomics applied in predicting patients who are at risk of developing immunotherapy-induced pneumonitis and radiation pneumonitis have shown promising results [20,38]. Based on these findings, future studies could focus on comparing predictive values of different imaging approaches, such as CT, ultrasound and bronchoscopy combined with artificial intelligence technology. In this ambispective cohort study, we developed and validated a novel model incorporating radiomic signatures and clinical signatures to provide an easy-to-use and individualized prediction of SI-ARDS occurrence and severe degree in patients at early stage. Moreover, research has indicated that immune microenvironment abnormalities play a critical role in SI-ARDS [39,40], revealing that disturbances of neutrophil migration and neutrophil apoptosis caused neutrophil accumulation in the lung tissues, resulting in lung injury. We considered and initially explored correlation between radiomic features and immune-associated inflammatory indicators.

This study has several limitations. First, there are intrinsic limitations and possible patient selection bias in this observational and partly retrospective cohort study. Since the majority of sepsis patients first receive a chest X-ray, those with a relatively high risk of ARDS would be referred for chest CT and those with severe septic shock would receive bedside chest radiograph. However, a subgroup analysis will be performed by comparing mild sepsis group alone (removing the septic shock subgroup) with the pulmonary and non-pulmonary sepsis group. Second, the follow-up duration is relatively short. However, this period is quite adequate for consideration of the early primary outcome of SI-ARDS. A third limitation is the relatively small sample size and that high-dimensional extracted radiomics features may result in model overfitting. Therefore, these available data still remain inconclusive and need to be further validated in future multicenter prospective studies.

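### Logistic p-values and unpenalised coefficients for variables already selected by random forest and LASSO would be over-optimistic if, as seems intended, both steps use the 160 discovery patients

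*Protocol article*

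**What the plan says.** Section 2.7 of the protocol article sets out a sequence.

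- **Selection.** Variables enter the regression after a consensus of two outcome-driven methods: "using variables that selected by consensus of variable importance ranking by random forest [28] and least absolute shrinkage and selector operation (LASSO) regression techniques".
- **Regression.** "Univariate and multivariate logistic regression will predict occurrence of ARDS".
- **Final models.** "With the selected clinical and radiomics features, we will develop two versions of the ARDS prediction model, using logistic regression (LR) and support vector machine".
- **Threshold.** The only significance level in the article is in this sentence: "All these algorithm performances will be assessed using the AUC and *p*-values less than 0.05 will be considered statistically significant".

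Section 2.1 names one set of patients for building the model: "One hundred-sixty patients of the retrospective cohort will be selected as a discovering group to reconstruct the model". It reserves 40 further retrospective patients for internal validation and 200 prospective patients for external validation. According to the Abstract, performance is judged by AUC, sensitivity and specificity. Among the limitations in section 3, the article notes that "high-dimensional extracted radiomics features may result in model overfitting".

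The article does not say on which patients the selection or the regressions run. It also does not say whether the logistic model is penalised, and it describes no sample splitting or selection-adjusted inference.

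**The concern.** Random forest and LASSO keep a variable because it is associated with ARDS in the data at hand. An ordinary logistic regression on the same patients then tests that association as if the variable had been named in advance. Its p-values are too small, and more so the larger the pool from which the variables were picked.

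The second consequence is for prediction. LASSO shrinks coefficients to offset overfitting, and an ordinary refit of the survivors removes that shrinkage. The coefficients become too large, so predicted risks move too far towards 0 and 1. Section 3 promises a prediction for the individual patient, so the size of the predicted risk matters as well as the ranking. AUC depends on ranking alone, and sensitivity and specificity on a single cut-off.

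At stake are any list of significant radiomic or clinical risk factors taken from the discovery data, and the individual risks from the logistic model.

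**Working it through.** **Inputs from the article.** Discovering group 160 (section 2.1). About 20 variables, 5-10 patients per variable and an ARDS rate of 25-50% (section 2.3). External group 200 (section 2.1).

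**Assumed inputs.** The number of candidate features before selection is not given; the features are only called high-dimensional. A range of 20 to 1000 was used.

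**Step 1, the plan's own figure.** The rule gives 20 × 5 = 100 to 20 × 10 = 200 patients. The stated 160 lies inside this range (160 / 20 = 8 per variable), but no stated input fixes 8. At 160 patients there are 160 × 0.25 = 40 to 160 × 0.50 = 80 ARDS events, or 40 / 20 = 2 to 80 / 20 = 4 events per variable. The article gives no figure for the error rate of p-values after selection, so there is none to reproduce.

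**Step 2, p-values after selection.** The simulation used 160 patients, independent pure-noise features, and 60 data sets per setting. A LASSO logistic path was stopped at about 20 features and intersected with the top 40 of a simplified random-forest ranking (bagged one-split trees). Wald tests at 0.05 followed on the same 160 patients, then on 200 new ones. Ranges cover ARDS rates of 25% and 50%.

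| Candidates (assumed) | Mean number selected | Univariate p<0.05, same patients | Multivariable p<0.05, same patients | At least one p<0.05 (multivariable) |
|---|---|---|---|---|
| 20 | 13.1 | 6-8% | 8-11% | 63-72% |
| 100 | 16.3-16.4 | 26-28% | 34-36% | 100% |
| 500 | 11.7-12.6 | 91% | 60-65% | 100% |
| 1000 | 10.2-10.5 | 99-100% | 74% | 100% |

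Multiplying the number selected by the multivariable share gives the average count of falsely significant features per study:

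- 20 candidates: 13.1 × 0.079 = 1.0 to 13.1 × 0.107 = 1.4
- 100 candidates: 16.3 × 0.343 = 5.6 to 16.4 × 0.358 = 5.9
- 500 candidates: 11.7 × 0.601 = 7.0 to 12.6 × 0.648 = 8.2

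For scale, 20 independent tests with no selection give 1 − 0.95^20 = 64% for at least one false positive. The 63-72% in the first row is therefore mostly ordinary multiplicity.

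A second simulation with LASSO selection alone, 100 or 500 candidates, and independent or correlated features put 28-65% of the selected noise features below 0.05. At 500 candidates the working range is about 50-65%.

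**Step 3, the same features in new patients.** Tested in 200 new patients, the selected noise features fell below 0.05 in 4.4-5.3% of univariate and 4.9-6.4% of multivariable tests, close to the nominal 5%.

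**Step 4, effect on individual risks.** With five true predictors among 100 or 500 candidates (both assumed) and 160 patients, the calibration slope in new patients was as follows (ideal value 1):

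- Independent features, log-odds 0.5 per SD assumed: 0.05-0.32 for the ordinary refit, 0.75-1.38 for the LASSO coefficients.
- Independent or correlated features: 0.06-0.44 for the refit, 0.79-1.43 for the LASSO coefficients.

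A slope well below 1 means that predicted risks are spread too widely.

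**The case against.** The strongest reply is that the plan does not do what a reader might infer from it. Several parts of that reply stand.

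- **No p-value rule for predictors.** A reader might infer that a coefficient p-value below 0.05 retains a feature or declares it a predictor. No sentence says so. Features are chosen by random forest and LASSO, the threshold is in the sentence on algorithm performance, and odds ratios and confidence intervals are never mentioned.
- **Same patients is an inference.** Section 2.7 names no analysis set, and a fuller protocol or analysis plan may do so. The inference is still strong: section 2.1 gives only the discovering group for building the model, and selecting or fitting in the other groups would spoil the validation.
- **The threshold keeps a meaning elsewhere.** A reader might infer that 0.05 is void throughout. It is not: a test in the untouched prospective patients keeps its level, and plain group comparisons are not post-selection tests of this kind.
- **The size depends on an unstated number.** With 20 candidates the inflation is slight. However, section 2.3 expects about 20 variables to be selected from the radiomic features, so a pool of only 20 is the least plausible case.
- **Prediction is judged in separate patients.** The AUC in the 200 prospective patients is an honest estimate for whatever model is frozen, and section 3 discloses the overfitting risk. The SVM does not depend on logistic p-values.
- **The unpenalised refit is also a reading.** The article does not specify it, but it is what logistic regression means when no penalty is named.

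The stated order of methods, with nothing in it to allow for the selection, is not answered by these replies. Univariate and multivariate logistic regression after selection usually yields coefficients with p-values, and 0.05 is the only threshold on offer for them. Disclosing overfitting does not correct it.

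**Conclusion.** The point holds in a limited form. Followed as written, with selection and fitting in the discovering group, the sequence gives anti-conservative p-values for the selected variables. The inflation is slight if there are about 20 candidates, roughly sevenfold at 100 (about 35% against 5%) and ten- to thirteenfold at 500 (50-65% against 5%). If the logistic model is an unpenalised refit, its individual risks would also be too extreme, and the planned performance measures would not show this directly.

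The conclusion rests on same-patient use, an ordinary refit and the assumed candidate counts. The exact percentages will differ with real, correlated radiomic features and a full random forest. The documents do not support the broader conclusions that noise features will be declared predictors or that the external validation is undermined. This should be corrected because it is cheap to do, but it does not invalidate the primary aim.

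**What to change.** Amend section 2.7, or the analysis plan, in four places:

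1. State that variable selection and model fitting use only the 160-patient discovering group. Section 2.2 speaks of a developing group of 200, so the set needs naming.
2. Carry the penalised (LASSO) coefficients into the logistic model in place of an unpenalised refit.
3. Omit discovery-group p-values for selected variables, or label them descriptive.
4. For claims about predictors, apply the 0.05 threshold only to the frozen score in the 200 prospective patients and, if wanted, to the frozen predictors there.

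Bootstrap selection frequencies and Firth regression for the individual predictors are optional additions.

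The cost is a few sentences and small code changes, with no new patients or data. The downside is that fewer predictors will be called significant.

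### Section 2.7 puts ventilator-free and respiratory failure-free days through the time-to-event methods that suit 28-day mortality; if deaths are then censored, recovery is overstated

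*Protocol article*

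**What the plan says.** Section 2.6 (Outcome Measures) lists four secondary outcomes. Three matter here:

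- "Ventilator-free days, VFD: defined as the number of days between successful weaning from mechanical ventilation and day 28 after ICU admission".
- "Respiratory organ failure-free days, RFFD", which is "defined as the number of days between a day without evidence of respiratory organ failure". Only one end of the interval is named.
- "28-day mortality: all-cause mortality within 28 days following enrolment". This is listed separately and is not combined with either day count.

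Section 2.7 (Statistical Analysis) treats the three together: "VFD, RFFD and 28-day mortality will be screened indicators with LASSO-COX and RFE-SVM algorithm". The next sentence is "Thereafter, these will be estimated using the Kaplan–Meier method", and then "All these algorithm performances will be assessed using the AUC". Earlier in the section, an ROC cut-off is chosen and "patients will be divided into high-risk and low-risk groups". The section opens with a general provision for t or Wilcoxon tests on continuous variables, which it does not link to VFD or RFFD. Neither section mentions a score for death, a competing event or cumulative incidence.

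**The concern.** Cox regression and Kaplan–Meier need a time and an event indicator. Mortality has both. A count of free days up to a fixed day has neither: each patient has a complete value, higher is better, and values gather at the ends of the scale. To run the stated pipeline, the analysts must therefore choose something that the plan does not give. They can put the count itself on the time axis, or they can change the outcome to time to weaning or recovery.

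The second choice carries the risk. A patient who dies on the ventilator can no longer be weaned, but standard Kaplan–Meier and Cox analyses censor that patient as though weaning could still happen later. The reported recovery proportion is then too high. A high-risk group that loses more patients before weaning can show the same recovery curve as a low-risk group that loses few. The comparison of risk groups on two of the four secondary outcomes would then miss the difference it is meant to show.

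**Working it through.** The plan gives no sample size, power or effect size for VFD or RFFD, so there is no figure of its own to reproduce. The check shows how large the effect is under the default treatment of deaths.

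**Inputs from the article.** Mortality of about 40% once ARDS has developed (Introduction); a 28-day window (section 2.6); 200 patients in the validating group (section 2.1).

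**Assumptions.** Constant daily hazards of weaning, w, and of death before weaning, d. For the range, w runs from 0.05 to 0.12 per day and deaths before weaning from 20% to 40%. The lower end is used because not every sepsis patient develops ARDS. For the test comparison, the 200 patients are split evenly, 100 per risk group, with two-sided tests at 0.05.

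**Formulas.**
- True proportion weaned by day 28: w/(w+d) × (1 − exp(−28(w+d))).
- One minus Kaplan–Meier with deaths censored: 1 − exp(−28w).
- One minus Kaplan–Meier with deaths kept at risk to day 28: equal to the true proportion.

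**Single group.**
- 60% weaned, 35% dead first: w+d = −ln(1 − 0.95)/28 = 0.1070; w = 0.1070 × 0.60/0.95 = 0.0676; Kaplan–Meier gives 1 − exp(−0.0676 × 28) = 84.9%, against a true 60%.
- 70% weaned, 20% dead first: w+d = −ln(1 − 0.90)/28 = 0.0822; w = 0.0822 × 0.70/0.90 = 0.0640; Kaplan–Meier gives 83.3%, against a true 70%.

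**Range.**

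| w per day | Deaths before weaning | True weaned | Kaplan–Meier, deaths censored | Excess (points) |
|---|---|---|---|---|
| 0.05 | 20% | 64.1% | 75.3% | 11.2 |
| 0.05 | 40% | 51.7% | 75.3% | 23.6 |
| 0.08 | 20% | 74.2% | 89.4% | 15.2 |
| 0.08 | 40% | 57.7% | 89.4% | 31.7 |
| 0.12 | 20% | 78.5% | 96.5% | 18.0 |
| 0.12 | 40% | 59.6% | 96.5% | 36.9 |

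**Two groups that differ only in deaths.** With w = 0.07 in both and d = 0.01 or 0.05, Kaplan–Meier gives 1 − exp(−1.96) = 85.9% in each group. The true proportions are 0.07/0.08 × (1 − exp(−2.24)) = 78.2% and 0.07/0.12 × (1 − exp(−3.36)) = 56.3%.

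**Effect on a test.** 2,000 simulated comparisons, 100 per group, w = 0.08 in both, deaths before weaning 20% and 40%. Mean VFD with death scored 0 is 14.8 and 12.2 days, a difference of 2.6 days. Rejection rates:
- log-rank, deaths censored: 5%, the nominal level;
- log-rank, deaths kept at risk to day 28: 51%;
- Wilcoxon on VFD with death = 0: 30%.

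With 30% deaths in both groups, all three reject about 5% of the time, as they should.

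**The case against.** The strongest reply is that the article does not say time to weaning will be modelled, nor that deaths will be censored. That is right. A reader might infer that the plan as written overstates recovery; the documents do not support that. The overstatement is a conditional consequence, and it disappears if deaths stay at risk to day 28.

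A reader might also infer that using the count as the time variable gives a meaningless curve or a reversed hazard ratio. It does not. For an uncensored count, Kaplan–Meier is the empirical survivor function, and a hazard ratio above 1 means fewer free days, the same direction as a mortality hazard ratio. The approach is unusual and prone to ties, but not shown to be invalid.

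Nor do AUC and RFE-SVM strictly force the count to be cut in two: support-vector methods exist for continuous outcomes, time-dependent AUC exists for Cox models, and the AUC sentence also covers the ARDS models, where it fits.

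The scenario behind the hidden difference is constructed. The hazards are not in the article, and the 40% mortality applies to established ARDS, whereas the cohort is sepsis patients, of whom section 2.3 expects 25–50% to develop ARDS. Fewer deaths before weaning mean a smaller excess. The difference in deaths would also appear in the separate 28-day mortality outcome. The severity outcome is the PaO2/FiO2 grade, so the severity classification is not undermined by this point. In the simulated scenario, Wilcoxon with death lowest was less sensitive than the test with deaths kept at risk.

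Two replies do not succeed. The general Wilcoxon sentence does not override the sentence that assigns VFD and RFFD by name to other methods, and it leaves the predictor screen untouched. Nor is this only a detail left to a fuller plan: section 2.7 names a method, and it does not match the outcome type in section 2.6.

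**Conclusion.** The point stands in a limited form. Section 2.7 gives three outcomes one time-to-event pipeline that fits only 28-day mortality, while section 2.6 defines VFD and RFFD as day counts and gives no rule for death. The mismatch is in the text. Its numerical consequence depends on a choice that the text leaves open. If time to weaning is modelled with deaths censored, the excess is about 11 to 37 points over the assumed range, and groups that differ only in deaths before weaning can show the same recovery curve. The sizes rest on constant hazards and the assumed rates; the direction, given censored deaths, does not. The correction is worth making before analysis because it is cheap, but it concerns two secondary outcomes. The primary outcome, ARDS occurrence, is modelled by logistic regression and SVM and is unaffected.

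**What to change.** 1. Complete the RFFD interval in section 2.6 first, with both end points and the window. Until then no method for RFFD can be judged.
2. In section 2.7, limit LASSO-Cox and Kaplan–Meier to 28-day mortality.
3. State that VFD and RFFD are analysed as ordered day counts with death given the lowest value. Compare high- and low-risk groups with the Wilcoxon test already named. For the predictor screen, use an ordinal or rank-based model (for example penalised proportional odds) and report the concordance index in place of AUC.
4. If time to weaning is also shown, use cumulative incidence with death as the competing event.

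The cost is wording in sections 2.6 and 2.7 and standard R functions. No data are needed beyond the weaning dates and vital status that the outcomes already require. The downsides are one more model type to report, and that scoring death lowest makes each count a composite of recovery and survival, which section 2.6 should say.
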